### Data collection

In online supplemental table 1, we detail what baseline and follow-up data will be collected to assess primary and secondary outcomes. During the economic evaluation, additional cost and process evaluation qualitative data will be collected.

10.1136/bmjopen-2025-109111.supp4Supplementary data

### Monitoring

The study will be monitored by the study management group and the University of Warwick representative of the Sponsor to ensure that the study is being conducted as per protocol, adhering to Research Governance and Good Clinical Practice (GCP). Central monitoring activities will be performed such as data quality checks. The recruiting site is obliged to assist the sponsor in monitoring the study. These may include hosting site visits, providing information for remote monitoring, or putting procedures in place to monitor the study internally. The approach to, and extent of, monitoring will be specified in a study monitoring plan determined by the risk assessment undertaken prior to the start of the study.

### Analysis

#### Statistical analysis plan

A detailed statistical analysis plan will be prepared by the statisticians and agreed with the study team, prior to final analysis, and which will follow the NICE RWE Framework.^29^ Comparisons will be primarily on an as-started (intention-to-treat, ITT) basis. We do not expect any or only minor levels of treatment switching or discontinuation for the W8Buddy group. Therefore, we would expect the on-treatment and as-started treatment effect estimates to be equivalent in this population. We will report the result according to the Strengthening the Reporting of Observational Studies in Epidemiology guideline.^30^

#### Summary of baseline data

Demographic and baseline data will be summarised overall and by treatment arms and sites. Categorical data will be summarised as count and percentage, and continuous data will be summarised as number of missing data, mean with SD, and median with 25th and 75th percentiles.

#### Missing data

Patterns of missing data/discontinuation will be reported and assessed if missingness was at random or provided useful information on treatment efficacy.

#### Primary and secondary outcome analysis

The primary analysis will compare temporal changes in weight for the W8Buddy and standard care group, from baseline to completion of follow-up (at 18 months), using longitudinal mixed effects regression models. The effectiveness of the W8Buddy will be quantified by differences in rates of weight change compared with standard of care during follow-up. All the secondary outcomes will be analysed individually with longitudinal mixed effects models.

For all analyses, we will consider adjusting for a range of demographics and clinical characteristics (eg, age, gender, ethnicity, Index of Multiple Deprivation/Welsh Index of Multiple Deprivation, comorbidities, NHS site, mode and distance of travel and other confounders identified using Directed Acyclic Graphs with stakeholders PPI members and members of the steering committee)^31^ using propensity-weighted longitudinal mixed models. We expect the fixed effects to be demographics and clinical characteristics as mentioned above and the random effects to be the sites and individuals. A sensitivity analysis using distance to NHS site as an instrumental variable^32^ will also be conducted to assess the assumption of no unmeasured confounders.

The comparison between the hybrid intervention and both the standard of care and fully digital intervention will be an unpowered secondary analysis, that we hope will offer additional insights and help to characterise the magnitude of intervention effects from the primary analysis.

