### Sample size calculation

We will collect weight data at baseline and a minimum of three occasions during the study, for both pathways. Powering the study to show that the digital pathway is non-inferior to the standard of care pathway, with a difference less than 4 kg, at 90% power and a two-sided 5% level, gives a sample size of approximately 180 participants. Further assuming a correlation between the repeated weight measurements in the range 0.2–0.5, which previously collected data suggests is reasonable,^28^ based on a longitudinal mixed model/repeated measures Analysis of covariance (ANCOVA) gives a total sample size of 360. Conservatively assuming 20% loss during follow-up, the target sample size is 450.

Given the current widespread use of the digital (W8Buddy) intervention at the lead centre (UHCW), the control (standard of care; SC) intervention at this site will be different from that offered at the other sites. For this reason, we plan to characterise the control intervention at UHCW as a ‘hybrid’ digital intervention. We will aim to recruit sufficient participants (ie, 360) at the three other sites (UHB, LLT, HDUHB) to fully power the study for the planned comparison between the digital and standard of care groups. Additionally, we will collect data from the ‘hybrid’ digital intervention at UHCW to augment and further refine the primary analysis.

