### Intervention Gro Health W8Buddy

Gro Health W8Buddy is a virtual specialist WMS pathway. It is accessed through a digital behavioural change platform called the Gro Health app (see, figure 2). Participants on the W8Buddy digital arm will receive 52 weeks of support from healthcare professionals employed by DDM. At week 52, each participant on the digital pathway will be assessed and the following options offered: discharge to primary care, onward referral to local tier 4 if interested in surgery, onward referral for local tier 3 MDT discussion, extension of digital pathway by 6 months, referral to local tier 2 WMS.

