### Outcomes

The primary outcome is changes in body weight after 18 months of using either (1) a fully digital weight management programme (remote digital pathway Gro Health W8Buddy) or (2) site-specific delivered weight management programmes incorporating face-to-face and/or virtual group sessions (standard care).

Secondary outcomes are metabolic markers (HBA1c, lipids), blood pressure, waist circumference and health-related QoL (EQ-5D-5L).^28^

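### The study is powered for non-inferiority within 4 kg at 18 months, but the primary effect is stated as a difference in rates of weight change and is never tied to that margin

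*Protocol article*

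**What the plan says.** Under Sample size calculation, the aim is given as "Powering the study to show that the digital pathway is non-inferior to the standard of care pathway". The margin and error rates stated there are "with a difference less than 4 kg, at 90% power and a two-sided 5% level". That section also names a longitudinal mixed model or repeated-measures ANCOVA, and it is the only place where non-inferiority or the margin appears.

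Under Outcomes: "The primary outcome is changes in body weight after 18 months of using either" the digital programme or site-specific standard care. This fits a margin in kilograms.

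Under Primary and secondary outcome analysis, longitudinal mixed models compare the course of weight from baseline to 18 months. The effect measure is then fixed: "The effectiveness of the W8Buddy will be quantified by differences in rates of weight change compared with standard of care during follow-up". No margin, conversion of the margin or rule for the conclusion follows.

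Under Intervention Gro Health W8Buddy: "Participants on the W8Buddy digital arm will receive 52 weeks of support from healthcare professionals employed by DDM". At week 52 the options include discharge, referral to other services, or a 6-month extension of the digital pathway.

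**The concern.** The margin is in kilograms and the stated effect is in kilograms per unit of time. To compare them, the analyst must either assume a constant rate of change over 18 months or depart from the stated effect measure. The article does neither.

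The conclusion of the study depends on this. A non-inferiority claim rests on a confidence bound lying inside the margin. An estimate of effectiveness expressed as a rate difference, with no margin, invites a reading by statistical significance, which answers a different question. A non-significant rate difference could then be taken as showing that the pathways are equally good, in a study meant to inform NICE and national adoption.

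**Working it through.** **1. The plan's own figures.** The last step reproduces: 360/(1 − 0.20) = 450. The first step ("gives a sample size of approximately 180 participants") cannot be checked, because no SD is given and the text does not say whether 180 is per arm or in total. Back-solving with SD = 4 × √(n/2)/(1.960 + 1.282), where n is the number per arm:
- 180 per arm: 4 × √90/3.2415 = 11.71 kg
- 180 in total (90 per arm): 4 × √45/3.2415 = 8.28 kg

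Both SDs are used below as assumptions, with 1:1 allocation.

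**2. The margin as a rate.** 4 kg/18 months = 0.222 kg/month, valid only if change is constant over the 18 months.

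**3. Can a rate difference and an 18-month difference disagree?** Assume weights at 0, 6, 12 and 18 months in both arms. These paths are invented to show the mechanism and do not predict this study.
- Arm A, loss then partial regain: 0, −5, −10, −5 kg.
- Arm B, steady loss: 0, −1.67, −3.33, −5 kg.

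The true difference at 18 months is 0. For a straight-line fit, the mean time is 9 and Sxx = 81 + 9 + 9 + 81 = 180.
- Arm A: Sxy = 0 + 15 − 30 − 45 = −60; slope = −0.333 kg/month; × 18 = −6.0 kg.
- Arm B: slope = −5/18 = −0.278 kg/month; × 18 = −5.0 kg.

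The scaled rate difference is −1.0 kg, a quarter of the margin, although the arms end level.

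**4. A difference test and a margin test answer different questions.** With 180 per arm, SE = SD × √(2/180).

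| Assumed SD | SE | Truly equal: P(upper limit < 4 kg) | Truly equal: P(significant difference) |
|---|---|---|---|
| 11.71 kg | 1.234 | Φ(4/1.234 − 1.96) = 90% | 5% |
| 8.28 kg | 0.873 | Φ(4/0.873 − 1.96) = 99.6% | 5% |

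If the digital pathway were truly 2 kg worse, both probabilities would be about 37% at SD 11.71 kg and 63% at SD 8.28 kg.

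**5. Does the sample size carry over to the rate scale?** Take the assumed SD as that of weight at one visit, with equal correlation between visits and no random slopes. The variance of slope × 18 is then SD² × (1 − ρ) × 18²/180, and n per arm = 2 × variance × 3.2415²/4². Over the stated range ("assuming a correlation between the repeated weight measurements in the range 0.2–0.5"), the totals are:

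| SD | ρ = 0.2 | ρ = 0.5 |
|---|---|---|
| 8.28 kg | 260 | 164 |
| 11.71 kg | 520 | 326 |

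These lie on both sides of the stated 360, so power on one scale cannot be assumed on the other.

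**The case against.** The strongest reply is that this is detail for the statistical analysis plan, which the article says will be prepared before the final analysis. A longitudinal mixed model fitted to 18 months can give an 18-month contrast with a confidence interval to hold against 4 kg. Much of this stands: the model is suitable, and a missing confidence rule alone would be no finding. But the article does not leave the effect measure open. It names one on a different scale from the margin. A later plan that follows that sentence needs an added constant-rate assumption to use the margin, and one that tests 4 kg at 18 months departs from the sentence.

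Stronger readings that a reader might infer are not supported:
- **Three conflicting targets.** The sample size and outcome sections are compatible, since 4 kg can apply to change at 18 months. The conflict is with the one sentence on rates.
- **A straight line is planned.** The text speaks of rates and never says linear. Step 3 shows what a constant-rate summary would do.
- **Regain after week 52 is to be expected.** A 6-month extension is among the options and would reach month 18, and the article gives no regain figure. Regain or plateau is possible, which is enough to make a constant rate doubtful.
- **The arms will be weighed on different schedules and bias the slope.** The article sets a minimum number of weights for both pathways and leaves the schedule to a supplement not shown. On arm A's path, monthly weights to month 12 plus month 18 would give slope × 18 = −8.65 kg instead of −6.00 kg, but unequal schedules in the analysis are not established.

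**Conclusion.** The point holds as a mismatch between the stated primary effect and the margin and outcome for which the study was sized. Followed literally, the primary analysis reports a rate difference that bears on the 4 kg margin only under an unstated constant-rate assumption (0.222 kg/month), which the change in support at week 52 makes doubtful. It would go too far to say that the planned analysis cannot deliver a non-inferiority conclusion: the same model can, once the effect and the rule are stated on the right scale.

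The size of any discrepancy in this study cannot be derived from the document. The 1 kg example rests on invented paths, and the probabilities and sample sizes rest on back-solved SDs and equal allocation. The mismatch itself depends on none of them.

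**What to change.** In the primary analysis section:
- State the primary effect as the propensity-weighted adjusted difference, digital minus standard, in weight change from baseline to 18 months.
- Estimate it from the planned longitudinal mixed model, with time modelled flexibly enough not to force a constant rate, for example visit as a category with treatment-by-visit terms.
- Conclude non-inferiority only if the upper limit of the two-sided 95% CI is below +4 kg.
- Report the difference in rates as secondary.

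Visit as a category is one acceptable choice; the essential change is an 18-month contrast tied to the margin.

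The cost is wording, plus a small loss of precision if change really is linear. As a guide, take complete data, three follow-up weights, equal correlation and baseline adjustment in both models. The variance multiplier for the 18-month contrast is 1 − ρ², which is 0.96 at ρ = 0.2 and 0.75 at ρ = 0.5. For a linear effect scaled to 18 months it is (1 − ρ)/[14/9 − 4ρ/(1 + 3ρ)], which is 0.758 and 0.662. The standard error would be larger by √(0.96/0.758) = 1.13 and √(0.75/0.662) = 1.06, that is, by 6% to 13%.

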We acknowledge the challenges that may occur with the adoption of a digital pathway into NHS sites such as recruitment rates, levels of engagement and differences in WMS at NHS sites. However, capturing any challenges that may arise and providing solutions will benefit the future implementation of W8Buddy and contribute to generalisable knowledge. Our design means that we will not have matched cohorts across treatment arms, meaning both known confounders (eg, age, BMI) and unknown factors may influence outcomes. To address this, our planned analyses will incorporate statistical adjustments to account for these differences as far as possible. We recognise the limitations of this approach, but it is consistent with the pragmatic design and will allow us to report findings that are representative of real-world practice.

We aim to improve NHS Specialist WMS services by facilitating the evidence generation and scale-up of digital innovation Gro Health W8Buddy. This could, in turn, support other NHS organisations wanting to deliver digitally enabled services. The findings of this study will be used to generate recommendations for other service providers, targeted education and creation of a virtual learning environment. It is aimed that the study outputs will provide evidence needed for full NICE technology appraisal, as well as evidence for NHS commissioners to facilitate national adoption of technology in specialist WMS.

10.1136/bmjopen-2025-109111.supp2Supplementary data

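### The one analysis named to assess unmeasured confounding, a distance-to-site instrument, is likely to be too imprecise to separate a bias that matters against the 4 kg margin from no bias

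*Protocol article*

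**What the plan says.** Under Primary and secondary outcome analysis, the protocol article plans propensity-weighted longitudinal mixed models adjusted for demographic and clinical characteristics. It adds a sensitivity analysis with distance to the NHS site as an instrument, which "will also be conducted to assess the assumption of no unmeasured confounders". No other analysis in the article is directed at unmeasured confounding. The Discussion accepts that the cohorts will not be matched, "meaning both known confounders (eg, age, BMI) and unknown factors may influence outcomes", and offers statistical adjustment in response.

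The Sample size calculation section powers the primary comparison for non-inferiority "with a difference less than 4 kg, at 90% power and a two-sided 5% level, gives a sample size of approximately 180 participants". It then assumes "a correlation between the repeated weight measurements in the range 0.2–0.5", which "gives a total sample size of 360", and finishes with "Conservatively assuming 20% loss during follow-up, the target sample size is 450". It also says "We will aim to recruit sufficient participants (ie, 360) at the three other sites", so the powered comparison excludes the lead centre. None of this sizing refers to the IV analysis. The article gives no outcome SD and no expected strength of association between distance and pathway choice.

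**The concern.** Propensity weighting and covariate adjustment deal with measured factors only. With a single instrument, the IV result bears on unmeasured confounding mainly through how far it departs from the adjusted estimate. An IV standard error is roughly the primary standard error divided by the correlation between instrument and treatment, so in a study sized for the primary contrast that departure is estimated much less precisely than the effect itself.

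Unless distance predicts choice strongly, the two estimates will usually look compatible whether or not self-selection has biased the result. A reader of the eventual report, including NICE, could take such a result as reassurance. What is at stake is how much weight the 4 kg conclusion can bear in a non-randomised comparison.

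**Working it through.** **Inputs from the article.** Margin 4 kg, power 90%, two-sided 5%, about 180 participants before and 360 after the repeated-measures step, 20% loss, target 450 (Sample size calculation).

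**Plan's own figure.** 360 / (1 − 0.20) = 450, which reproduces. The 180 cannot be checked because no SD is stated. Inverting the non-inferiority formula gives an SD of about 8.28 kg if 180 is a total, or 11.7 kg if it is per arm (360 in total).

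**Primary standard error.** Three values cover the uncertainty:
- 4 / (1.960 + 1.282) = 1.23 kg: the design's own precision if 360 delivers 90% power with no true difference.
- 2 × 8.28 / √360 = 0.87 kg: 360 analysed with the smaller SD.
- 0.65 kg: a further reduction if three weights are averaged. The variance factor (1 + 2ρ)/3 is 0.47 at ρ = 0.2 and 0.67 at ρ = 0.5, so the SE is about 0.60 to 0.71 kg, and 0.65 is a mid value.

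**Assumptions.** A fully valid instrument, equal arms, no variance inflation from weighting, and the effect expressed as a kg difference at 18 months. The first three favour the check.

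**Formulas.** Let R² be the share of variance in pathway choice explained by distance, and r its square root.
- SE of IV estimate = SE / r
- SE of (IV − primary) = SE × √(1/R² − 1)
- A two-sided 5% comparison detects bias b half the time when b = 1.96 × SE of the difference, so the break-even is R² = SE² / [SE² + (b/1.96)²]
- Bias that moves the limit from an observed zero difference to 4 kg = 4 − 1.96 × SE

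Example at SE 1.23 and b = 4: 1.523 / (1.523 + 4.165) = 0.27.

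| SE (kg) | Break-even R², 4 kg bias | Bias moving the limit to 4 kg | Break-even R² for that bias |
|---|---|---|---|
| 1.23 | 27% | 1.58 kg | 70% |
| 0.87 | 15% | 2.29 kg | 36% |
| 0.65 | 9% | 2.73 kg | 18% |

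**Chance of missing a 4 kg bias** at assumed values of r:

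| r (R²) | IV 95% half-width at SE 1.23 | Missed, SE 1.23 | Missed, SE 0.87 | Missed, SE 0.65 |
|---|---|---|---|---|
| 0.2 (4%) | 12.1 kg | 90% | 85% | 76% |
| 0.3 (9%) | 8.1 kg | 83% | 70% | 51% |
| 0.5 (25%) | 4.8 kg | 54% | 25% | 6% |

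With 360 participants, r = 0.2 gives a first-stage F of 358 × 0.04 / 0.96 = 14.9. A customary F > 10 screen would therefore pass an instrument that misses a 4 kg bias in 76% to 90% of cases.

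**Simulation.** A Durbin-Wu-Hausman test was simulated with n = 360 and a true 4 kg inferiority fully masked by confounding. With SD 11.7 kg, non-inferiority was declared in about 90% of runs. Among those, the check missed the bias in 93%, 90%, 81%, 64% and 45% at R² of 2%, 5%, 10%, 20% and 30%. With SD 8.28 kg the misses were 90%, 81%, 66%, 39% and 14%.

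**The case against.** The strongest reply is that the article writes no decision rule. It promises a sensitivity analysis, not a Hausman test, a 5% threshold or an agreement criterion. A reader might infer that a non-significant difference will be taken as proof of no bias, but the text does not say so, and an IV estimate shown with a wide interval would reveal its own imprecision. This stands. The working shows what such a comparison could detect, not a rule the authors adopted.

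Second, detail is deferred to a statistical analysis plan that is to follow the NICE real-world evidence framework and is not shown. A reader might infer that the trial has no other safeguard. That does not follow: the IV analysis is the only one named in this article, and the later plan may add more. What remains is that the article already fixes the purpose of the IV analysis, and that purpose asks more than the study size is likely to support.

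Third, it is tempting to say the check would usually fail whatever happens. The documents do not support that without conditions. With SE 0.87 kg and r = 0.5, a 4 kg bias is caught about 75% of the time.

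Fourth, 1.58 kg might be read as enough to make digital care inferior. It is not. It brings the confidence limit to 4 kg, while the corrected difference of 1.58 kg stays well inside the margin. From an observed zero, a true difference at the margin requires a bias of about 4 kg.

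Finally, the authors disclose non-random allocation and unknown factors as limitations. That is fair and lowers the risk of over-claiming, but it does not make the check more precise.

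**Conclusion.** The concern holds in conditional form. The single analysis that the article names for unmeasured confounding is likely to be too imprecise for that purpose, because nothing in the sizing provides for it. A 4 kg bias would be missed more often than not unless distance explains more than about 27% of the variance in pathway choice at SE 1.23 kg, 15% at 0.87 kg, or 9% at 0.65 kg. For the smaller bias that only brings the confidence limit to 4 kg, the thresholds are about 70%, 36% and 18%.

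These figures assume a valid instrument, equal arms and no loss of precision from weighting; unequal uptake or variable weights would raise the thresholds. Instrument strength and SD are assumptions, since the article gives neither. Separately, the same section lists travel distance among the variables to consider adjusting for. Those two uses need reconciling, but the result here does not depend on that. The point is a low-cost improvement to the analysis and does not show that the primary analysis is wrong.

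**What to change.** In Primary and secondary outcome analysis, and in the statistical analysis plan that follows it:

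- Keep the distance-based IV estimate as supportive. Report its first-stage strength and a confidence interval for its difference from the primary estimate.
- State that the lack of a detectable difference is not evidence of no unmeasured confounding.
- Add a bias analysis that reports, in kg, the unmeasured confounding needed to move the unfavourable confidence limit for digital versus standard care to 4 kg.
- Set that figure beside the shift in the estimate when each strong measured confounder (for example BMI, comorbidities, deprivation) is left out of the propensity model. Leave the comparison to judgement, without a pass/fail robustness rule.

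The cost is some wording and slightly more analysis of data already being collected, with no extra participants or visits. The downside is that the robustness statement may turn out less favourable than a report that the IV analysis agreed.
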